## Methods

### Study design

A randomised controlled trial with three parallel arms will be conducted to examine the effectiveness of Strataderm® topical silicone gel, pressure garment therapy, and combined topical silicone gel and pressure garment therapy for the prevention and management of burn scars in children. Individual randomisation by patient will be undertaken using computer-generated random numbers. Randomisation will occur using a 1:1:1 ratio between groups in blocks of 12 and will be stratified by surgical intervention received (i.e. skin grafting in the acute phase, spontaneous skin healing in the acute phase, post-acute reconstructive surgery). Concealment of treatment allocation will be completed by the use of sealed, opaque, identical and serially numbered envelopes prepared in advance by an independent party. All outcomes will be measured at baseline (scar intervention commencement), 3 months and 6 months post burn or reconstruction. The primary outcome measures and the level of pressure beneath pressure garments will also be measured at 1 week post baseline. This project has ethics approval from the Child Health Queensland Human Research Ethics Committee (HREC). A flow diagram of the data collection process is displayed in Fig. 1.

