### Participants

#### Inclusion criteria

The inclusion criteria are children with a burn injury who are managed in the acute phase post burn (up to 16 years of age, as per current practice) or who receive burn scar reconstructive surgery (up to 18 years of age, as per current practice) at the participating burns centre and who require attendance at a scar management clinic after skin healing. Children who receive skin grafting, children with wounds that have not healed by day 17 post burn and children receiving surgery for burn scar reconstruction in all body locations with a TBSA burned of less than or equal to 40% who are accompanied by a parent or guardian, who is able to provide informed consent, will be eligible for inclusion. Up to two scar sites per person will be recruited where possible with both sites receiving the same intervention. Children with a cognitive impairment that impedes their ability to communicate will be enrolled in the study, however, they will not be required to complete self-report measures. Children and their families who do not speak English will be approached to participate in the study with the use of an interpreter but will only have objective scar measures and the itch Numeric Rating Scale (NRS) administered.

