### Outcome measures

#### Primary outcome measures

Scar itch intensity and scar thickness will be measured as primary outcomes. *Itch intensity* will be self-reported for children aged 5 years and older using an 11-point NRS (0 to 10). The Toronto Pediatric Itch Scale is an observation-based scale rating itch behaviours on a scale of 0 (absence of itch) to 4 (severe itch with significant disruption) and will be completed by caregivers for children aged under 5 years [20]. Caregivers for children of all ages will also complete the itch item of the Patient and Observer Scar Assessment Scale (POSAS, 0 to 10 NRS). Numeric rating scales have been recommended over visual analogue scales due to improved adherence, increased responsiveness and fewer missing values in populations of adults with pain and chronic itch [34, 35]. Numerical testing will be conducted with all children aged under 8 years and any children known to have learning difficulties to ensure they have the capacity to use the NRS [36].

*Scar thickness* will be measured using the GE Healthcare ultrasound. The GE Healthcare ultrasound system has been found to have an intraclass correlation coefficient (ICC) of greater than 0.90 for test-retest reliability when used with children with burn scars [37]. When measuring scar thickness with the GE Healthcare ultrasound, an image will be taken centrally from the site of interest (as opposed to peripherally on the scar border). An average of three measurements will be recorded and used in the analysis.

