### Statistics

#### Sample size

The sample size estimate was calculated based on the primary outcome of scar thickness at 6 months post burn for one scar site. We assumed a pooled standard deviation of 1.0 mm based on a retrospective audit of data from our centre. To detect a statistically significant between-group difference of 0.76 mm in scar thickness with 80% power and an alpha value of 0.017 (due to three pairwise comparisons), 36 participants are required in each of the three groups. Assuming a 20% dropout, the total number of participants who need to be recruited at baseline is 135 (45 participants per group).

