The primary outcomes will be analysed using mixed effects regression analyses to examine differences at 6 months post burn, adjusting for the baseline value of the outcomes. Mixed effect regression analyses will be completed for each follow-up time point. Potential confounding variables that are identified as imbalanced between the groups will be entered into regression analyses. The time-varying covariates are patient adherence, level of pressure beneath garments, and other interventions received. All of the other potential confounding variables are non-time-dependent covariates. Sensitivity analyses will be completed for missing data using multiple imputation of missing observations by creating ten complete data sets [49] of missing dependent and independent data. For participants from whom data is collected from two scar sites, the multiple sites on these individuals will be accounted for in analytic models by including the scar site as a random effect nested within participant. Initially all participants will be included in the analyses. The analyses will then be repeated after stratifying by surgical intervention (i.e. skin grafting in the acute phase, spontaneous skin healing in the acute phase, post-acute reconstructive surgery). Subsequently, the influence of sociodemographic, clinical and intervention factors, and primary and secondary outcomes not included as dependent variables, on primary and secondary outcomes will also be examined using regression models. Differences in health-related quality of life between the intervention group and respective normative comparison groups will be analysed using *t* tests, z-scores, or equivalent nonparametric tests where appropriate. Differences in self-reported outcomes by children versus caregivers, between age groups and in comparison to normative data will also be examined using univariate statistics such as *t* tests, z-scores, or nonparametric equivalents. Significance will be set at less than 0.05. Data will be analysed using SPSS (SPSS Inc., Chicago, IL, USA) or Stata (StataCorp, College Station, TX, USA) where appropriate.

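### One model per visit leaves the earlier scans of children missing at 6 months out of the main 6-month estimate, and makes the site-within-participant variance redundant with the residual

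*Protocol article*

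**What the plan says.** All places are in the protocol article.

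- **Visits (Study design).** "All outcomes will be measured at baseline (scar intervention commencement), 3 months and 6 months post burn or reconstruction". In addition, "The primary outcome measures and the level of pressure beneath pressure garments will also be measured at 1 week post baseline". Each primary outcome therefore has up to three post-baseline values.
- **Model (Data analysis).** "The primary outcomes will be analysed using mixed effects regression analyses to examine differences at 6 months post burn, adjusting for the baseline value of" [each outcome]. The next sentence is "Mixed effect regression analyses will be completed for each follow-up time point". Adherence, in the same section, is also compared visit by visit with linear regression. No visit effect, arm-by-visit term or repeated-measures structure is described.
- **Two scars on one child.** Under Inclusion criteria: "Up to two scar sites per person will be recruited where possible with both sites receiving the same intervention". The Data analysis section says that multiple sites are accounted for by "including the scar site as a random effect nested within participant".
- **Values per site and visit (Primary outcome measures).** For thickness, "An average of three measurements will be recorded and used in the analysis". One number per site and visit enters the model.
- **Missing data (Data analysis).** Multiple imputation with ten data sets is a sensitivity analysis. The benefit analysis is called intention-to-treat, but it keeps only children who finish follow-up data collection and receive the full recommended duration of treatment.
- **Attrition (Sample size).** "Assuming a 20% dropout, the total number of participants who need to be recruited at baseline is 135", that is, 45 per group for 36 evaluable.

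**The concern.** Two things follow if each visit has its own model.

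First, the main 6-month estimate rests on the children seen at 6 months, adjusted for baseline. The 1-week and 3-month values of the others, already collected, are not used. The estimate is then safe only if missing the 6-month visit is unrelated to how the scar looked at 3 months, given baseline and arm. One can imagine that failing here. The Discussion expects adherence to differ between gel and garments, and attrition could differ with it.

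Second, the stated random-effects structure does not fit a one-visit model. With one value per site, site and residual are the same level. The term belongs to a model with several visits, which the text does not describe. An analyst following the text would have to choose between the two.

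**Working it through.** **1. The plan's own figure.** Inputs from Sample size: difference 0.76 mm, SD 1.0 mm, alpha 0.017 (two-sided reproduces), power 80%.

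n per group = 2 × ((2.387 + 0.842) / 0.76)² = 36.09, stated as 36. Then 36 / 0.8 = 45, and 3 × 45 = 135. The figure reproduces. Power at 36 per group is 79.9% by the normal approximation (78.0% with the noncentral t). It rests on one site and the 6-month value, with dropouts counted as lost, so the point below does not change it.

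**2. Site variance in a one-visit model.** Let P, S and E be the participant, site and residual variances.

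- One visit: variance of a value = P + S + E; covariance of two sites on one child = P. There are two moments for three unknowns. P and the sum S + E are determined; the split between S and E is not.
- Several visits in one model: covariance of the same site at two visits = P + S; of different sites = P; variance = P + S + E. There are three moments for three unknowns.

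Numerical check (illustrative: 36 children, half with two sites, P = 0.5, S + E = 0.5):

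| S | E | log-likelihood, one visit |
|---|---|---|
| 0 | 0.5 | -73.543 |
| 0.25 | 0.25 | -73.543 |
| 0.4 | 0.1 | -73.543 |
| 0.5 (just below) | 0 (just above) | -73.543 |

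The information matrix for P, S and E has rank 2 of 3 with one visit and rank 3 of 3 with two. With P and one combined lower-level variance, one visit gives rank 2 of 2. The standard error of an arm contrast depends only on P and S + E, so it is unaffected by the arbitrary split.

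**3. Precision from using 3-month values.** Assumptions, not in the protocol: correlation r between 3 and 6 months given baseline; n3 children per arm seen at 3 months, including all 36 seen at 6 months; missingness completely at random. Any further gain from 1-week values is not counted.

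Variance of the arm mean (SD 1) = (1 − r²)/36 + r²/n3, and effective n is its inverse.

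| r | n3 | variance | effective n | variance saved against 1/36 |
|---|---|---|---|---|
| 0.5 | 40 | 0.75/36 + 0.25/40 = 0.02708 | 36.9 | 2.5% |
| 0.5 | 45 | 0.75/36 + 0.25/45 = 0.02639 | 37.9 | 5.0% |
| 0.8 | 40 | 0.36/36 + 0.64/40 = 0.02600 | 38.5 | 6.4% |
| 0.8 | 45 | 0.36/36 + 0.64/45 = 0.02422 | 41.3 | 12.8% |

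Over a wider range (r from 0.3 to 0.9, with half or all of the nine missing children seen at 3 months), effective n runs from 36.4 to 43.0. By the normal approximation, power is 79.9% at 36, 82.3% at 38 and 84.4% at 40 per arm.

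**4. Bias when dropout depends on the 3-month scar.** Assumed: logistic dropout with slope 1 per SD of the 3-month value, which gives 21% missing. At SD 1.0 mm the complete-case 6-month mean of that arm is off by -0.05, -0.09, -0.13 and -0.16 mm for r = 0.3, 0.5, 0.7 and 0.9. Against the 0.76 mm target that is 0.054/0.76 = 7% to 0.161/0.76 = 21%. Using the 3-month value brings the error to about zero. These are shifts in one arm's mean; to the extent that the same shift occurs in the other arms, it cancels in the contrasts.

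**The case against.** The case on the other side has several parts.

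- **Separate models are inferred.** The word does not appear. The section also distinguishes time-varying from fixed covariates and nests site in participant, both of which suit a longitudinal model with a contrast at each visit. This is fair, but it does not rescue the text. A one-visit model can use that visit's adherence or pressure value. If a longitudinal model was meant, the per-visit sentence misdescribes it and the visit terms are absent.
- **The article is condensed.** Covariance structure may well be left to an analysis plan. That is true of the detail, but whether there is one model or one per visit is something the article itself addresses.
- **Imputation is planned.** It covers missing dependent data and could draw on earlier visits. This stands in part: the values need not be lost to the trial, only to the main analysis. The text does not say that earlier visits enter the imputation.
- **Dropout is budgeted for.** The 36 evaluable per group already assumes that these children are lost. This stands: planned power is not reduced.
- **A joint model has its own risk.** With random intercepts alone it forces equal variance and equal correlation across unevenly spaced visits, and could misstate the 6-month standard error. This stands and shapes the fix.

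A reader might also infer that the plan ignores the correlation between two scars on one child, so that standard errors are too small and the type I error is inflated. The protocol does not support that. It says that multiple sites are accounted for, and nesting in participant implies a participant effect. With that effect fitted, the clustering is handled and the superfluous site term costs at most a convergence warning.

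**Conclusion.** The point holds as a modest, worthwhile correction. On its natural reading the plan leaves usable post-baseline data out of the main 6-month estimate, and it states a variance component that its one-visit model cannot estimate. On the other reading, the model description contradicts itself. Either way the Data analysis section needs rewording.

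The precision gain is about 3% to 13% of variance. It depends on assumed correlations of 0.5 to 0.8 and on 40 to 45 children per arm being seen at 3 months; neither figure is in the protocol. The protection against bias may matter more, but its size depends on a dropout mechanism that is assumed here and on that mechanism differing between arms. The redundant site term does not by itself bias the treatment effect or its standard error, and the sample size is unaffected. Changing the model alone would not bring the missing children back, because the completer restriction also removes them.

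**What to change.** 1. For scar thickness, and for each itch scale on its own metric, state one longitudinal mixed model for all post-baseline visits: arm, visit, arm-by-visit, baseline value with its visit interaction, and surgical stratum. The 6-month arm contrasts are primary; earlier visits are secondary.
2. Include random intercepts for participant and for site within participant, and allow residual variances and correlations to differ by visit, unstructured where estimable. A fully unstructured covariance across visits within a site already contains the site intercept. In that case drop the site intercept and keep the participant intercept, so that the redundancy does not return.
3. Redefine the intention-to-treat set as every randomised child with at least one post-baseline value, analysed in the allocated arm.
4. If a single-visit model is kept as a check, use a participant random intercept only.
5. If multiple imputation is kept as a sensitivity analysis, say that 1-week and 3-month values enter the imputation model.

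The cost is analysis wording only: no new data, and the named packages, SPSS and Stata, fit such models. The downside is a slightly more complex model and reliance on its covariance structure, so a fallback structure should be named in advance in case the preferred one does not converge.

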#### Data analysis

Sociodemographic, clinical and intervention data will be summarised using descriptive statistics. For continuous outcomes either mean and standard deviation, or median and range will be used depending on the distribution of the variable. For categorical outcomes frequency and percentage will be reported. Data related to intervention benefits will be analysed on the ‘intention-to-treat’ (ITT) principle, defined as participants analysed according to their randomly allocated study group regardless of treatment received who complete follow-up data collection and who receive the recommended length of intervention. Data related to intervention adverse effects will be analysed according to the ITT principle as well as per protocol defined as those who received and commenced the intervention. A sensitivity analysis will be conducted to compare the ITT and per-protocol approaches if appropriate. Baseline characteristics will be compared to assess the compatibility of groups. At baseline between-group differences will be investigated using linear regression for continuous data and Fisher’s exact test for categorical data. Post-baseline, between-group differences in adherence will also be investigated using linear regression at each time point. Potential confounding variables for the primary outcomes are considered a priori to be: age, days to re-epithelialisation, percentage maximum burn depth, days post burn when scar management commenced, Fitzpatrick skin type, percentage TBSA burned, patient adherence, level of pressure beneath garment (for the groups treated with pressure garments), anatomical body site treated, surgical intervention received (skin grafting in the acute phase, spontaneous wound healing in the acute phase, post-acute reconstructive surgery), wound complications (e.g. infection), other interventions received (e.g. massage) including the use of medications for itch [8, 9, 48].

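### Covariates enter the primary model only if found imbalanced, which in practice drops the surgical stratum used in randomisation and leaves the rest of the adjustment set to chance

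*Protocol article*

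**What the plan says.** Study design (protocol article): "Randomisation will occur using a 1:1:1 ratio between groups in blocks of 12 and will be stratified by surgical intervention received". The three strata are grafted in the acute phase, healed spontaneously in the acute phase, and post-acute reconstruction.

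Data analysis: the mixed model for the primary outcomes is fitted "adjusting for the baseline value of the outcomes". That is the only covariate entered unconditionally. The section then lists twelve potential confounders, surgical intervention among them, and gives the entry rule: "Potential confounding variables that are identified as imbalanced between the groups will be entered into regression analyses". On how imbalance is looked for, it says: "At baseline between-group differences will be investigated using linear regression for continuous data and Fisher’s exact test for categorical data". No threshold for calling a variable imbalanced is given; the general significance level in the section is 0.05.

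The stratum has one other use: after the all-participant analysis, the analyses are repeated within each surgical group.

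**The concern.** Two things go wrong under this rule.

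First, stratified blocks exist to prevent imbalance on surgical intervention. A rule that admits only imbalanced variables therefore shuts out the one factor the design singled out. The protocol itself treats that factor as prognostic: Background lists skin grafting and delayed healing among the risk factors for scarring, and Confounding factors names surgical intervention first. When randomisation is balanced on a prognostic factor and the model omits it, the between-stratum variance stays in the residual although it no longer contributes to the variance of the treatment contrast. The model-based standard error is then too large, confidence intervals are too wide, the test runs below its nominal size, and power is lost.

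Second, differences in pre-randomisation variables between randomised arms are due to chance, so testing them says nothing about which variables are worth adjusting for. What makes adjustment useful is the strength of the covariate's relation to the outcome. Under the rule, the content of the primary model is unknown until the data are seen, and with no stated threshold it also depends on judgement.

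**Working it through.** **Inputs from the Sample size section.** SD 1.0 mm, difference 0.76 mm, alpha 0.017 per pairwise comparison, 80% power, 36 evaluable per arm, 20% dropout, 135 recruited.

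**The plan's own figure.** Two-sided normal approximation: n = 2(2.387 + 0.842)² / 0.76² = 36.1 per arm, against 36 stated (37 if rounded up). Power at 36 is 79.9%. With dropout, 36/0.8 = 45 per arm and 3 × 45 = 135. The sample size reproduces and is not in dispute.

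**Can the stratum be flagged?** A block of 12 holds four of each arm, so within a stratum two arms can differ by at most four children, and only through an unfinished last block. In a simulation of 135 children with stratified blocks of 12 (assumed stratum shares 35/50/15%), a chi-square test at 0.05 of stratum by arm, standing in for Fisher's exact test, flagged the stratum in 0% of runs.

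**Cost of omitting it.** Let R² be the share of outcome variance left after baseline adjustment that the stratum explains. The documents give no value, so 0.1, 0.2 and 0.3 are assumptions. The 1.0 mm SD is used as the residual SD before the stratum is entered.

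- Model SE without the stratum: √(2/36) = 0.2357 mm. True SE: 0.2357 × √(1 − R²). Ratio: 1/√(1 − R²).
- True size of the nominal 0.017 test: 2[1 − Φ(2.387/√(1 − R²))].
- Power, stratum omitted: Φ[(0.76 − 2.387 × 0.2357) / (0.2357√(1 − R²))] = Φ[0.837/√(1 − R²)].
- Power, stratum included: Φ[0.76/(0.2357√(1 − R²)) − 2.387] = Φ[3.224/√(1 − R²) − 2.387].

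| R² | SE ratio | True size | Power, omitted | Power, included |
|---|---|---|---|---|
| 0.1 | 1.054 | 0.012 | 81% | 84% |
| 0.2 | 1.118 | 0.008 | 83% | 89% |
| 0.3 | 1.195 | 0.004 | 84% | 93% |

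**Check by simulation.** Same set-up with 20% random dropout, total SD 1.0 and t-based tests (8,000 runs under the null, 4,000 under 0.76 mm):

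| R² | Size, omitted | Size, included | Power, omitted | Power, included |
|---|---|---|---|---|
| 0 | 0.019 | 0.018 | 78% | 78% |
| 0.1 | 0.014 | 0.018 | 79% | 83% |
| 0.2 | 0.011 | 0.019 | 80% | 88% |
| 0.3 | 0.006 | 0.016 | 81% | 91% |

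The formula assumes exact balance; dropout leaves small imbalances, so the simulated test is a little less conservative. The direction is the same, and the power gain is about 4, 8 and 11 points against 3, 6 and 9 by formula.

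**Chance selection of the rest.** Of the twelve listed candidates, three are named as time-varying (adherence, garment pressure, other interventions) and one is the stratum, leaving 12 − 3 − 1 = 8. If these are independent and tested at 0.05, P(at least one flagged) = 1 − 0.95⁸ = 0.337.

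**The case against.** The best reply is that the protocol does not exclude the stratum. It is a listed candidate, the analyses are repeated within surgical groups, and a statistical analysis plan that is not shown could add it to the model. The harm is also bounded: omission does not bias the estimate, the test errs on the conservative side, and simulated power without the stratum stays at roughly the planned 80%.

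Some of this stands. The damage from omission is lost precision, not bias. The size of the loss depends on an R² that the documents do not give; if baseline thickness already carries the stratum information, it could be close to nil. Unfinished blocks are possible, and so is loss that depends on arm and stratum, particularly because the analysis set is restricted to children who complete follow-up and the recommended length of treatment. The 0% flag rate therefore holds for random dropout and the assumed stratum shares. The 0.05 threshold is inferred from the baseline tests, and correlated candidates, such as burn depth and healing time, would generally bring the 34% down.

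The main point is not answered. The text states a rule, and an analysis plan that follows it inherits the problem. Being a candidate does not put the stratum in the model. The repeats by surgical group give subgroup results and leave the primary estimate and its standard error unchanged.

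One qualification runs the other way. The chance argument covers variables fixed before randomisation. Adherence, garment pressure and other interventions are observed afterwards, and the protocol's Discussion expects adherence to differ between treatments. Imbalance in these may be an effect of treatment, so letting the same rule admit them could bias the comparison.

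**Conclusion.** The concern holds. As written, the rule keeps the randomisation stratum out of the primary model in practice and leaves the other baseline adjustments to chance findings. If the stratum explains 10% to 30% of the remaining variance, the primary standard error is 5% to 20% too wide. The nominal 0.017 test then runs at 0.012 to 0.004 by formula (0.014 to 0.006 simulated), and about 3 to 9 points of power are given up (4 to 11 simulated). Confidence is high on the rule and the direction of its effect. The size is conditional on the assumed R², with no gain at zero. This should be changed, though it does not threaten the validity of the unadjusted comparison.

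**What to change.** State the primary model in advance: treatment arm, baseline value of the outcome and surgical stratum, always included. Add a short named list of pre-randomisation prognostic factors that are already collected, kept in whatever their balance. Age and days to re-epithelialisation are natural examples. Days from burn to start of scar management is another, but its time origin would need defining for reconstruction patients, whose follow-up is counted from surgery. The stratum is the essential addition; the rest of the list is a matter of choice, provided it is fixed before the outcome data are seen.

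Remove imbalance as the entry criterion, drop baseline significance tests as a selection rule, and present baseline data descriptively. Say explicitly that adherence, garment pressure and other post-randomisation variables are not in the primary model; they can be examined in separate, labelled analyses.

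The cost is wording and a few degrees of freedom (two for the stratum). No new data are needed and the sample size does not change.
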